### Data collection and management

Patient data will be prospectively collected using standardized Case Report Forms (CRFs) and entered into a secure REDCap electronic database. Baseline demographic and clinical characteristics, biomarker data, imaging-based tumor response, adverse events, concomitant medications, and biomarker samples will be recorded according to the study schedule (Table 2).

An independent Data Monitoring Committee (DMC), consisting of clinical epidemiologists, data monitors, and statisticians not involved in trial conduct, will review study safety, data completeness, and protocol deviations at regular intervals. The DMC charter specifies the composition, responsibilities, meeting schedule, and decision-making procedures. Based on these reviews, the DMC may recommend continuation, modification, or termination of the trial.

All source documents and biological samples will be stored securely and retained for at least 5 years after study completion in accordance with institutional and regulatory requirements.

Data sharing: Anonymized individual participant data will be shared upon reasonable request after publication, in accordance with applicable data protection regulations and participant consent.

Patient and public involvement: No patients or members of the public were involved in the design, conduct, or reporting of this trial.

### Statistical analysis

The statistical analysis will be performed using SAS statistical software (version 9.4). The primary analyses for efficacy and safety will be conducted according to the Intention-to-Treat (ITT) principle, including all randomized participants in the groups to which they were assigned. A per-protocol (PP) analysis will also be performed as a supplementary analysis.

#### Handling of missing data

For the primary endpoint (PFS), censoring will be applied at the last known follow-up date for patients without a progression event. For other continuous variables with missing values, multiple imputation will be used for primary analyses, with sensitivity analyses using Last Observation Carried Forward (LOCF).

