#### Follow-up and assessments

Follow-up visits will occur every 3 months, as outlined in Table 2, and will include clinical evaluation, imaging studies, laboratory testing, and assessment of adverse events. Imaging for tumor response assessment will be performed every 8 weeks from randomization until disease progression. The efficacy of YFXJD will be evaluated through progression-free survival, TCM symptom scores, activity levels, biochemical parameters, and exploratory biological indicators. Safety will be assessed according to protocol-defined criteria. The trial flowchart is presented in Figure 1.

**Table 2 tab2:** Schedule of trial.

Assessment/Time point	Screening	Baseline/Initiation	Treatment period	Treatment period	Long-term follow-up	End-of-treatment visit	Survival follow-up
	D -7	D0	D90 ± 7	D180 ± 7	D365 ± 7	Upon PD/Discontinuation	
Procedures							
Informed consent	✓						
Eligibility review	✓						
Data collection							
Demographic information	✓						
History of NSCLC & treatment	✓						
History of other diseases	✓						
Randomization & drug dispensing		✓	✓ (Re-supply)	✓ (Re-supply)			
Primary endpoints							
1. PFS (RECIST 1.1)			Imaging per protocol	Imaging per protocol	Imaging per protocol	✓ (Confirm PD)	Record death
2. TCM Syndrome Score	✓ (Baseline)		✓ (Interim)	✓ (Primary Time Point)			
Secondary endpoints (Efficacy)							
Tumor response (ORR/DCR)			✓	✓	✓	✓ (Final)	
Quality of life (EORTC QLQ)	✓ (Baseline)		✓	✓	✓		
Performance status (KPS)	✓ (Baseline)		✓	✓	✓		
Biomarkers							
Lymphocyte subsets	✓ (Baseline)		✓	✓	✓		
Inflammatory cytokines	✓ (Baseline)		✓	✓	✓		
Tumor markers	✓ (Baseline)		✓	✓	✓		
Safety assessments							
Clinical laboratory tests							
CBC, hepatic & renal function	✓	✓	✓	✓	✓	✓	
Urinalysis & stool routine	✓	✓	✓	✓	✓	✓	
AE/SAE collection	✓	✓	✓	✓	✓	✓	
EGFR-TKIs specific AE recording		✓	✓	✓	✓	✓	
Concomitant medication record		✓	✓	✓	✓		
Proportion with dose Mod./Disc.			Recorded	Recorded	Recorded	✓ (Final)	
Study administration							
Protocol deviation record		✓	✓	✓	✓		
CRF completion		✓	✓	✓	✓	✓	

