### Withdrawal/termination criteria

Participants will be withdrawn or terminated from the trial if any of the following conditions are met:Failure to adhere to the key procedures outlined in the study protocol, which may compromise the validity of the data obtained from that participant.The use of concomitant therapies that are prohibited by the protocol for the management of NSCLC or its symptoms.Discontinuation of osimertinib due to toxicity: Occurrence of severe adverse reactions attributable to osimertinib therapy that necessitate the permanent discontinuation of the targeted agent, as determined by the treating physician. This criterion focuses on adverse events (e.g., severe interstitial lung disease, hepatotoxicity, or intolerable grade 3/4 rash or diarrhea) that make continued osimertinib treatment unsafe.Withdrawal of consent: The participant voluntarily decides to withdraw from the study at any time for any reason.Loss to follow-up: The participant becomes unreachable or fails to attend scheduled study visits without providing reason, despite repeated attempts at contact by the research team.The principal investigator determines that continued participation is not in the best interest of the participant’s health and safety.

Participants who are discontinued from the study intervention will be encouraged to continue in the follow-up phase for the collection of survival and safety data, where feasible and with their consent. All reasons for withdrawal or discontinuation will be documented in the case report form.

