### Outcomes

#### Primary outcomes

Progression-Free Survival (PFS): Defined as the time from randomization to the first occurrence of radiographic disease progression according to RECIST 1.1 (15) criteria or death from any cause, whichever occurs first. Imaging will be performed every 8 weeks from randomization until disease progression, with blinded independent central review.

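### PFS is censored at last known follow-up, not at the last evaluable tumour assessment, so unscanned contact time counts as progression-free; the text on imaging after discontinuation and on deaths needs reconciling

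*Protocol article*

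**What the plan says.** All references are to the protocol article.

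- **Handling of missing data** fixes the censoring date of the primary endpoint: "For the primary endpoint (PFS), censoring will be applied at the last known follow-up date for patients without a progression event".
- **Primary outcomes** defines the event as "radiographic disease progression according to RECIST 1.1 (15) criteria or death from any cause, whichever occurs first", and adds: "Imaging will be performed every 8 weeks from randomization until disease progression, with blinded independent central review".
- **Follow-up and assessments** puts clinic contact on a different clock from the scans: "Follow-up visits will occur every 3 months, as outlined in Table 2". It repeats that imaging is 8-weekly until progression.
- **Table 2** has an end-of-treatment visit headed "Upon PD/Discontinuation", followed by a survival follow-up column. In that column the PFS row asks only for death to be recorded.
- **Withdrawal/termination criteria** says that participants who discontinue the study intervention "will be encouraged to continue in the follow-up phase for the collection of survival and safety data", where feasible and with consent. Tumour imaging is not named.
- **Sample size** expects a dropout rate of about 20%.

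**The concern.** A PFS time is informative about progression only as far as the patient has been scanned. The date of last known follow-up can be a clinic visit, a safety contact or a survival check, and each of these can fall after the last scan. Under the stated rule the patient stays in the risk set, counted as progression-free, up to that contact. Progressions in the unscanned interval are never seen and become event-free time.

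The patients most exposed are those who leave treatment without progression but remain in contact. For them the document gives two signals. The outcome and follow-up sections promise scans until progression. The withdrawal section and the last column of Table 2 mention survival, safety and death only.

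The wording raises a second point. The endpoint counts "criteria or death from any cause, whichever occurs first", while the censoring sentence applies to anyone without a progression event. Taken alone, that sentence would censor a death without prior progression.

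At stake are the absolute PFS estimates in both arms and, if withdrawal differs between arms, the hazard ratio of the primary analysis.

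**Working it through.** The document gives no figure for the effect of the censoring rule, so there is none to reproduce. The size has to be worked out from its design figures plus assumptions.

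**Inputs from the document (Sample size):** control median PFS 18.9 months; target hazard ratio 0.66; 12 months of accrual and 12 months of minimum follow-up, so follow-up at the data cut is spread evenly over 12 to 24 months; dropout about 20%.

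**Assumptions not in the document:** exponential PFS; dropout means leaving the scan schedule, reached by 18 months at a constant rate and independent of progression; the share of withdrawn patients who remain in contact (varied below).

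**Step 1: hazards per month.** Progression in control: λ = ln 2 / 18.9 = 0.03667. Withdrawal: w = −ln(0.80) / 18 = 0.01240. Sum: 0.04907.

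**Step 2: what the control curve shows if every withdrawn patient is known alive to the data cut.** A progression is then observed only if it precedes withdrawal, so the apparent PFS is

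S*(t) = 1 − [λ/(λ+w)] × [1 − exp(−(λ+w)t)], with λ/(λ+w) = 0.03667 / 0.04907 = 0.7474.

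- Median: setting S* = 0.5 gives exp(−0.04907 t) = 1 − 0.5/0.7474 = 0.3310, so t = 1.1056 / 0.04907 = **22.5 months**, against 18.9.
- 18-month PFS: true value exp(−0.03667 × 18) = 51.7%; apparent value 1 − 0.7474 × (1 − 0.4134) = 56.2%, an inflation of about 4.5 percentage points.

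**Step 3: hazard ratio, by simulation** (400,000 patients per arm, true hazard ratio 0.66). The milder case assumes that half of the withdrawn patients remain in contact, that median survival after progression is 12 months, and that those later deaths count as events.

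| Withdrawn by 18 months, control / YFXJD | Censored when scanning stops | Last contact, all known alive to cut | Last contact, half in contact, later deaths counted |
|---|---|---|---|
| 20% / 20% | HR 0.66, control median 18.9 | HR 0.66 to 0.67, control median 22.5 | HR 0.66, control median 20.0 |
| 15% / 25% | HR 0.66 | HR 0.62 | HR 0.65 |
| 25% / 15% | HR 0.66 | HR 0.71 | HR 0.67 to 0.68 |

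With only a quarter of withdrawn patients in contact, the two unequal cases read about 0.65 and 0.67, close to the true 0.66.

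**Step 4: the passages side by side.** On imaging after discontinuation, two sections say until progression, with no exception for patients off treatment. The withdrawal section and the survival column of Table 2 name no imaging. On deaths, the endpoint definition and the PFS row of Table 2 both count them; only the censoring sentence leaves them out.

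**The case against.** The strongest reply has four parts.

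*Scans may continue.* A reader might infer that withdrawn patients get no further scans. The document does not say so: no sentence stops imaging at withdrawal, and recording death only is also what one would expect of a column that follows progression. If 8-weekly scans are kept and attended, the last contact falls less than 8 weeks after the last scan and the rule does little harm. This stands. What remains is that the sections are not aligned, and that the rule still fails for anyone who misses scans but stays in contact.

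*Deaths are already events.* A reader might infer that deaths will be censored. The endpoint definition and Table 2 say otherwise, and a progression event can be read as shorthand for a PFS event. This is a wording conflict, not evidence that deaths will be dropped.

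*The hazard ratio is safe under equal withdrawal.* Correct. The only dropout figure is an overall one. A reader might infer that unequal withdrawal is likely because the herbal product could change tolerability, but nothing in the document gives withdrawal by arm, and the trial is double-blind with the same background drug in both arms. The 15% / 25% splits are illustrations, and they move the hazard ratio in opposite directions. A reader might also see a breach of intention-to-treat. There is none: a censoring date removes nobody from the analysis and moves nobody between arms.

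*The comparator is idealised.* Censoring when scanning stops looks unbiased in the table because withdrawal was drawn independently of progression. If withdrawal is related to prognosis, last-assessment censoring is informative too. This also stands, and is why both rules should be reported.

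None of this rescues the stated date. It is a rule that the document fixes, not a detail left to an analysis plan.

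**Conclusion.** The point holds in a limited form. The primary endpoint is censored at a date that does not match how progression is observed, and two pieces of nearby text (imaging after discontinuation, and the status of deaths) need to be brought into line.

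At 20% withdrawal in each arm, absolute PFS is overstated: a control median of about 20 to 22.5 months instead of 18.9, with no material bias in the hazard ratio. At 15% against 25%, either way round, a true 0.66 reads about 0.62 to 0.65 or 0.67 to 0.71, in favour of the arm with more withdrawals. The outer values are upper bounds, since they need every withdrawn patient to be unscanned and known alive at the data cut. For patients who withdraw consent or are lost, last contact lies near the last visit and the two rules nearly coincide.

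I rate this as something that should be fixed, not as a flaw that invalidates the trial.

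**What to change.** 1. Replace the censoring sentence under Handling of missing data with: *Patients without RECIST 1.1 progression or death are censored at the date of the last evaluable tumour assessment on or before the data cut (randomization date if none); deaths without documented progression are events.* This settles the wording on deaths as well.
2. Keep censoring at last contact as a sensitivity analysis.
3. Reconcile Withdrawal/termination criteria and Table 2 with Primary outcomes and Follow-up and assessments, so that the document says in one voice whether the imaging already planned until progression continues after study treatment stops.

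The cost is a few sentences and, as a protocol amendment, approval by the ethics committee. The censoring change needs no additional scans. There are two downsides: slightly less nominal follow-up time, and possible informative censoring if withdrawal is related to prognosis, which the sensitivity analysis helps to expose. There is time to act: Trial status reports 38 patients enrolled by July 2026 and final follow-up projected by December 2027. Scans that were not done cannot be recovered later, and a change of rule after unblinding would not be credible.

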#### Secondary outcomes

Change in TCM Qi-Yin Deficiency Syndrome Score: The absolute change in the total score from baseline to 6 months (D180 ± 7), assessed using a pre-specified and validated TCM syndrome scale specific for Qi-Yin deficiency in lung cancer. The scale ranges from 0 to 48, with higher scores indicating more severe symptoms. The minimal clinically important difference (MCID) is 4 points. All TCM assessors will undergo a 2-day training session with standardized patients, and inter-rater reliability (kappa ≥ 0.80) will be established prior to study initiation.Objective Response Rate (ORR) and Disease Control Rate (DCR) as per RECIST 1.1 (15).Duration of Response (DOR).Overall Survival (OS).Change in health-related quality of life assessed using the European Organization for Research and Treatment of Cancer Quality of Life Questionnaire Core 30 (EORTC QLQ-C30) (16) and its lung cancer-specific module (QLQ-LC13) (17).Change in Karnofsky Performance Status (KPS) score (18).Incidence, type, severity, and relationship to study treatment of all Adverse Events (AEs) and Serious Adverse Events (SAEs), graded according to the National Cancer Institute Common Terminology Criteria for Adverse Events (NCI CTCAE) Version 5.0 (19).

Evaluation of EGFR-TKIs-related specific adverse reactions:Rash: A validated skin toxicity assessment tool (e.g., HFSR-14 scale or specialized assessment based on CTCAE v5.0 dermatology criteria) will be used to record the incidence, maximum severity (grade), time to onset, duration, and management measures (e.g., topical/systemic medications, dose modifications) of rash.Diarrhea: The incidence, maximum severity (graded per CTCAE v5.0 gastrointestinal criteria), duration, frequency of diarrhea will be recorded, along with the proportion of patients requiring EGFR-TKIs dose modification, interruption, or discontinuation due to diarrhea. The use of anti-diarrheal medications will also be documented.The proportion of patients requiring EGFR-TKIs dose reduction, interruption, or permanent discontinuation due to the above or any other AEs.Changes in serum levels of inflammatory cytokines (IL-2, IL-6, IL-10, TNF-*α*, IFN-*γ*).Changes in peripheral blood lymphocyte subsets (CD3^+^, CD4^+^, CD8^+^, CD4^+^/CD8^+^ ratio, NK cells).Changes in serum tumor marker levels (CEA, CYFRA21-1, SCC-Ag, NSE).

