#### Comparative analyses

Between-group comparisons of continuous variables will use the independent samples t-test or Mann–Whitney U test, as appropriate. Categorical variables will be compared using the Chi-square test or Fisher’s exact test. For repeated measures (TCM syndrome score, QoL), baseline-adjusted mixed models for repeated measures (MMRM) will be used, with treatment group, visit, treatment-by-visit interaction, and baseline value as fixed effects, and participant as random effect.

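### LOCF, the named sensitivity analysis for missing TCM and quality-of-life scores, does not probe the missing-at-random assumption behind their main analyses

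*Protocol article*

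**What the plan says.** Under Handling of missing data, the protocol article states that for continuous variables other than PFS "multiple imputation will be used for primary analyses", "with sensitivity analyses using Last Observation Carried Forward (LOCF"). Under Comparative analyses, for the TCM syndrome score and quality of life, "baseline-adjusted mixed models for repeated measures (MMRM) will be used". Under Statistical analysis, "A per-protocol (PP) analysis will also be performed as a supplementary analysis"; that changes the population and does not test a missing-data assumption.

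The outcome most affected is the change in TCM Qi-Yin deficiency score at D180, on a 0 to 48 scale where higher is worse. Secondary outcomes states: "The minimal clinically important difference (MCID) is 4 points".

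Two places bear on which scores will exist. Table 2 schedules the TCM score at screening, D90 and D180, and quality of life at those visits and D365. Neither is ticked at the end-of-treatment visit (progression or discontinuation) or in survival follow-up. Withdrawal/termination criteria says that participants who stop the intervention "will be encouraged to continue in the follow-up phase for the collection of survival and safety data"; symptom and quality-of-life scores are not named.

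**The concern.** A sensitivity analysis for missing data should relax the assumption on which the main analysis depends. Here that assumption is MAR: after conditioning on observed data, patients without a score are taken to resemble those with one. The plausible threat is that patients whose scores are missing after progression are worse than this predicts.

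LOCF does not address that threat. For a patient who progresses before D180 it normally inserts the D90 score, or the baseline score (change of zero) if progression comes before D90. Both precede the event that makes worsening plausible, so LOCF returns much the same answer whether or not patients deteriorate afterwards. If it agreed with multiple imputation, the report could call the TCM and quality-of-life findings robust when the relevant question had not been asked.

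**Working it through.** The plan gives no figure for missing continuous data, so there is none to reproduce. The steps below size the issue.

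**Inputs from the Sample size section.** Median PFS is 18.9 months (control) and 28.6 months (YFXJD). **Assumptions.** PFS is exponential; a month is 30.4375 days; scores are missing once a patient has progressed or died; post-progression worsening is 4, 8 or 12 points (1, 2 or 3 MCIDs).

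**Step 1. Share progressed or dead by each visit**, p(t) = 1 − exp(−ln 2 × t / median). D180 is 180 / 30.4375 = 5.914 months.

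| Visit | Control | YFXJD |
|---|---|---|
| D90 | 10.3% | 6.9% |
| D180 | 19.5% | 13.4% |
| D365 | 35.6% | 25.2% |

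**Step 2. Arm difference that goes unseen at D180.** With no other change in scores, worsening of w shifts each arm's true mean by w × p. LOCF and MAR imputation both miss this shift. The missed difference (YFXJD minus control) is w × (0.1335 − 0.1950) = −0.0615w:

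- w = 4: −0.25
- w = 8: −0.49
- w = 12: −0.74

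Within an arm the miss is larger: at w = 12, 12 × 0.195 = 2.3 points in control and 12 × 0.1335 = 1.6 in YFXJD.

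**Step 3. Simulation.** 100 patients per arm, 2,000 runs, assumed SD 8 and between-visit correlation 0.6, no direct treatment effect. Within-arm regression imputation stands in for the multiple-imputation point estimate. Entries are YFXJD minus control in D180 change; negative favours YFXJD.

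| On-treatment drift | w | Full data | LOCF | MAR imputation |
|---|---|---|---|---|
| 0 | 4 | −0.23 | 0.02 | 0.03 |
| 0 | 8 | −0.52 | 0.00 | −0.01 |
| 0 | 12 | −0.73 | 0.00 | 0.00 |
| −4 | 0 | 0.03 | −0.16 | 0.02 |
| −4 | 4 | −0.25 | −0.20 | −0.01 |
| −4 | 8 | −0.53 | −0.23 | −0.04 |
| −4 | 12 | −0.74 | −0.19 | 0.00 |

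Without drift, LOCF and MAR imputation agree and both miss the difference. With drift, LOCF stays near −0.2 whatever w is. It is close to the full-data value at w = 4 only by coincidence.

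**Step 4. Bias that LOCF adds when MAR is true.** With a linear drift of −4 (−2 by D90), patients lost before D90 forgo 4 points of improvement and those lost between D90 and D180 forgo 2. Per arm that is 4 × p(D90) + 2 × [p(D180) − p(D90)] = 2 × [p(D90) + p(D180)]. Control: 2 × (0.103 + 0.195) = 0.60. YFXJD: 2 × (0.069 + 0.134) = 0.41. The difference is about −0.19, and simulation gives values close to this. It is a small spurious advantage for YFXJD.

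**Step 5. What a delta adjustment would show.** If unobserved YFXJD scores alone were 4 or 8 points worse than MAR predicts, that arm's mean would shift by 0.1335 × 4 = 0.53 or 0.1335 × 8 = 1.07. At 20% missing (the planned dropout rate) the shift is 0.8 or 1.6.

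**The case against.** **The main analyses do not rest on LOCF.** Inference on these scores comes from multiple imputation and MMRM, PFS is the primary outcome in the text, and exploratory secondary results are declared hypothesis-generating. All of this stands and limits the point to a minor one. Table 2 does list the TCM score among primary endpoints, but that inconsistency is a separate matter.

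**The bias is not caused by LOCF.** This stands for Step 2: MAR imputation misses the same amount, because the scores are not observed. The figure shows what the planned pair of analyses cannot detect, not the harm of choosing LOCF over multiple imputation.

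**A reader might infer that LOCF would produce a false positive for YFXJD.** The worsening scenarios without drift do not support that: the missed difference favours YFXJD, so its benefit is understated. Only Step 4 runs the other way, by about 0.2 points.

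**A reader might infer that LOCF standard errors are too small by about 9%**, from √(1 − 0.164) = √0.836 = 0.914. That does not hold. An LOCF value uses only the patient's own data, so patients remain independent and the usual standard error is valid for the LOCF contrast. In simulation with no drift (4,000 runs) the LOCF difference had an actual SD of 0.967 against a mean reported standard error of 0.965, with rejection near 5%. LOCF does leave out imputation uncertainty, but no 9% figure follows.

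**The missingness is inferred.** The article nowhere says that scores stop at progression; D90 and D180 visits carry no such condition. The inference rests on the empty cells in Table 2 and on the follow-up purpose, "for the collection of survival and safety data, where feasible and with their consent". Scores will also be lost through consent withdrawal and loss to follow-up, so the percentages in Step 1 are progression or death, not a forecast of missing scores.

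**The SAP may add more.** It may, and the absence of further analyses is not the point. The article itself names LOCF, and that choice can be judged.

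**Conclusion.** The point holds as a minor one, confined to the continuous secondary outcomes. LOCF is a poor sensitivity analysis here: its agreement with multiple imputation does not support MAR, and its disagreement does not refute it.

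Under the assumed worsening of 4 to 12 points, the arm difference that both methods would miss at D180 is about 0.25 to 0.7 points, or 6% to 18% of the 4-point MCID, in the direction of understating YFXJD. Under MAR with an assumed 4-point on-treatment improvement, LOCF itself adds a bias of about −0.2. These sizes depend on exponential PFS at the planning medians, on scores being missing after progression, and on the assumed worsening and drift, none of which the article gives for these scores. The argument that LOCF does not vary the MAR assumption needs none of these values. PFS and the main multiple-imputation and MMRM analyses are unaffected.

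**What to change.** Replace LOCF as the sensitivity analysis, or keep it only as a supplementary analysis, and specify one of the following on the imputation model already planned:

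- **Delta-adjusted (tipping-point) multiple imputation.** Worsen the imputed post-discontinuation scores in steps, for example 0, 4 and 8 points on the TCM scale, with delta varied separately by arm, and report where the conclusion changes. Set a corresponding grid for quality of life.
- **Reference-based imputation**, with YFXJD patients' scores after discontinuation imputed from the control arm.

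State how patients who die before the visit are handled, since a delta-adjusted symptom score after death has no clear meaning.

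The cost is a few lines of text and a little extra programming. No new patients, visits or data are needed. Database lock is planned for Q1 2028, so the change can be prespecified while the trial is still blinded.
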